# PROPENSIX: pressure garment therapy using compressive dynamic Lycra^®^ sleeve to improve bi-manual performance in unilateral cerebral palsy: a multicenter randomized controlled trial protocol

**DOI:** 10.1186/s13063-022-06041-1

**Published:** 2022-02-05

**Keywords:** Cerebral palsy, Upper limb, Children, Splint, Orthotic device, Randomized controlled trial, Placebo, Pressure garment therapy, Compressive dynamic Lycra^®^ sleeve, Bimanual performance

## Abstract

**Background:**

Upper limb impairment affects activity and participation in children with unilateral cerebral palsy (UCP). Pressure garment therapy (PGT) using compressive dynamic Lycra^®^ garments is an innovative intervention proposed for the management of cerebral palsy consequences. The PROPENSIX study aims to evaluate the efficacy of a therapy using a Lycra^®^ sleeve as compared to a placebo sleeve to improve bi-manual performance measured by the Assisting Hand Assessment (AHA) in children with unilateral cerebral palsy.

**Methods:**

The PROPENSIX trial is a multicenter, prospective, placebo-controlled, double-blinded, randomized study. One hundred children with UCP, aged from 5 to 10, are randomly assigned as soon as they are recruited in a 1:1 ratio to perform usual daily activities, especially activities involving bimanual performances, with Lycra^®^ sleeve or placebo sleeve during 6 months. The primary endpoint is the change in bimanual performance from inclusion to 6 months, evaluated by AHA. The secondary endpoints evaluate changes from inclusion to 6 months in other dimensions of the International Classification of Functioning (ICF), upper limb movement capacity assessed by Quality of Upper Extremity Skill Test (QUEST), and health-related quality of life evaluated by Pediatric Quality of Life Inventory 3.0 Cerebral Palsy Module (PedsQLTM 3.0 CP Module) and in body structures and functions domain assessed by neuro-orthopedic examination and somatosensory evoked potentials (SEP).

**Discussion:**

The PROPENSIX study is the largest randomized controlled trial (RCT) aiming to evaluate the efficacy of a PGT using compressive dynamic Lycra^®^ sleeve in UCP. Enhancement of children’s bimanual performance at the end of the 6 months wear of the Lycra^®^ sleeve should improve evidence regarding this type of treatment and expand discussion about their recommendation in clinical practice. Data from secondary outcomes assessments should bring interesting arguments to discuss the Lycra^®^ sleeve action on mobility, tonus, and sensory impairments in children with unilateral cerebral palsy.

**Trial registration:**

ClinicalTrials.govNCT02086214. Retrospectively registered on March 13, 2014

**Trial status:**

Study start data: December 2012. Recruitment status: completed. Primary completion date: April 2021. Estimated study completion date: December 2022. Protocol version 10 (date: February 2018).

## Introduction

Cerebral palsy is a neurodevelopmental disorder caused by nonprogressive lesions in the immature brain occurring before, during, or after birth. It is the most common physical disability in childhood, with a stable prevalence of 2 per 1000 live births [1]. Unilateral cerebral palsy (UCP) represents 20 to 30% of spastic cerebral palsy [2].

Arm and hand dysfunctions are the main problems in UCP. These troubles depend on several factors, including the extent of sensory loss, severity of paresis, degree of spasticity or presence of retractions, and whether or not dystonic movements are present [3]. It is estimated that 40 to 90% of children with spastic UCP have impaired somatosensory function [4,5]. Correlations between the magnitude of somatosensory dysfunction and movement impairments have been established [6,7]. Abnormal processing of somatosensory stimuli is suspected to contribute to poor cortical feedback during probabilistic learning of movement, providing imprecise or incorrect inferential data [8–10].

Cerebral palsy affects every dimension of the International Classification of Functioning (ICF). This framework is now guiding the evaluation and management of the children’s disability. Upper limb dysfunction is considered to be the main impairment that limits activity and restricts participation in hemiplegic children. Recent reviews and meta-analyses provide evidence-based arguments to guide the management of cerebral palsy [11–13]. The most frequently cited interventions for upper limb management are constraint-induced movement therapy (CIMT), bimanual training, interventions using new technologies (virtual reality and computer-based training therapy intervention), and botulinum toxin combined with specific interventions [14]. Splinting is one of the usual treatment strategies in cerebral palsy. Static, semi-dynamic, and dynamic splints are used among several purposes: prevent deformities, improve posture and movement, and facilitate functional performance [15].

Among dynamic splints, pressure garment therapy (PGT) is an innovative therapy using compressive dynamic Lycra^®^ garments. Lycra^®^ is a synthetic elastane fiber used in the confection of tailor-made close-fitting garments. The Lycra^®^ fabric is used to create a constant pressure and deliver a neutral heat on the concerned body part. Mechanical properties of Lycra^®^ garments have been established in studies involving healthy and hemiplegic adult subjects [16,17]. In children with cerebral palsy, previous studies advocate that pressure garment therapy (PGT) using compressive dynamic Lycra^®^ garments can improve postural alignment, joint stability, and movement efficiency and can enhance posture, balance, coordination, gross motor function, hand function, and gait of children with cerebral palsy and other health conditions [18–23]*.* The interest for using compressive dynamic Lycra^®^ garments reside in the fact that they are soft in nature and provide support while allowing movement.

Several mechanisms are proposed to explain how Lycra^®^ garments act. They are thought to decrease spasticity by prolonged stretch and cutaneous stimulation from tight skin contact which provides neutral heat. By decreasing hypertonia in spastic muscles, Lycra^®^ sleeve utilization on the impaired upper extremity should allow a better control of antagonist muscles (elbow and wrist extensors for example). In addition, the homogenous pression applicated by Lycra^®^ garments can modulate the sensory input and improve the sense of joint position and body awareness by stimulating mechanical receptors [20,24]. Despite nearly 30 years of research, pressure garment therapy has a low level of evidence in cerebral palsy management. One main reason is the lack of large randomized controlled trials (RCT). More studies are needed, especially high-quality studies focusing on functioning, in all dimensions of the ICF perspective.

In children with asymmetric impairments, wearing a compressive dynamic Lycra^®^ sleeve could bring a better utilization of the impaired arm, facilitate bi-manual coordination, and support learning of better motor patterns. Wearing this device while practicing bimanual activities (during school, playing, and eating activities) should result in a better improvement in bi-manual performance than practicing bi-manual activities alone. Inherent properties of Lycra^®^, such as homogenous compression, applied on the impaired upper limb of children should allow them to perform more accurate motor patterns, notably by an action on movement sensory-motor integration.

PROPENSIX study aims to evaluate efficacy of a PGT using a compressive dynamic Lycra^®^ sleeve as compared to a placebo sleeve to improve bi-manual performance measured by the Assisting Hand Assessment (AHA) in children with UCP.

## Methods and design

Table 1 summarizes the trial registration data and information about the study design and population.

**Table 1 Tab1:** Trial registration data, design of the study, and enrollment criteria

Data category	Information
Primary registry	ClinicalTrials.gov: NCT02086214, registered on March 13, 2014
Secondary identifying numbers	ANSM ID-RCB number: 2011-A01129-32 Ethics committee: CPP 12/05
Sponsor	Lille University Hospital
Contact	Maison Régionale de la Recherche Clinique, CHU Lille, [name] [contact] Mail : [contact]
Short title	PROPENSIX study
Scientific title	PROPENSIX: Pressure Garment Therapy using compressive dynamic Lycra^®^ sleeve to improve bi-manual performance in unilateral cerebral palsy, a multicenter randomized controlled trial
Country of recruitment	France
Inclusion criteria	Unilateral cerebral palsy (perinatal or antenatal etiology), 5 to 10 years old, social insurance, written informed consent
Exclusion criteria	Allergy to Lycra^®^, contra-indication to pressure therapy (e.g., skin lesions, allergic contact dermatitis), behavior or speech troubles, Botulinum Neurotoxin received within the 4 preceding months on the impaired arm, tutorship or curatorship, predictable lack of compliance
Intervention	Treatment: Lycra^®^ sleeve (Medical Z^®^, pressure = 15 to 25 mmHg) Placebo: Placebo sleeve (Medical Z^®^, pressure < 5 mmHg)
Study type	Interventional
Study design	Prospective, randomized, placebo-controlled, parallel assignment, double-blinded, multicenter, superiority trial
Target sample size	100
Primary outcome	Performance, evaluated by AHA (Time frame: 6 months)
Secondary outcomes	Capacity, evaluated by QUEST (Time frame: 6 months) Body structures and functions, evaluated by SEP and neuro-orthopedic examination (Time frame: 6 months) Participation, evaluated by PedsQL^TM^ 3.0 CP Module (Time frame: 6 months)
Estimated primary completion date	April 2021

*AHA* Assisting Hand Assessment, *QUEST* Quality of Upper Extremity Skill Test, *PedsQL™ 3.0 CP Module*: Pediatric Quality of Life Inventory 3.0 Cerebral Palsy Module

### Ethical considerations and trial registration

This clinical trial is approved by the Ethics Committee of Lille (Comité de Protection des Personnes Nord-Ouest IV, Lille University Hospital, N° CPP 12/05) and the French competent authorities (ANSM, N° 2011-A01129-32). It is registered at ClinicalTrials.gov under identifier NCT02086214 [25].

According to the Declaration of Helsinki, written informed consent is obtained from both parents of the child before enrollment. On the consent form, participants will be asked if they agree to use their data should they choose to withdraw from the trial. Participants will also be asked for permission for the research team to share relevant data with people from the Universities taking part in the research or from regulatory authorities, where relevant. This trial does not involve collecting biological specimens for storage. The consent form and information material are written in French and are available on request, from the corresponding author.

This protocol follows French regulations regarding biomedical research on medical devices. The trial sponsor did not judge necessary to establish a Data Safety Monitoring Board regarding the absence of specific risk. Serious adverse reactions are collected during the whole course of the trial and systematically reported to the principal investigator and safety department of the clinical trial sponsor. Any modification to this protocol is agreed by the ethics committee before implementation and notified to the health authorities in accordance with local rules.

### Trial design

PROPENSIX is a multicenter, prospective, double-blinded, randomized, placebo-controlled superiority trial using a medical device. The seven French study centers involved are specialized in pediatric rehabilitation. Both parents/children and physicians/therapists are blinded regarding the type of sleeve (active or placebo) used during the whole duration of the trial. Un-blinding will be performed for statistical analysis since it is needed for safety outcome comparison between the groups. Primary aim statistical analysis will be also un-blinded as adherence level is mandatory for future intention-to-treat and per-protocol statistical analysis.

Enrollment into the PROPENSIX study started in December 2012 and has been completed since September 2020. The clinical phase of the study was completed in April 2021. The coding process (neurologic exams, AHA, QUEST, and quality of life tests) and data handling are ongoing until the end of 2022.

Subjects are enrolled by the investigator of each study center. The randomization is centralized. The randomization sequence was provided by an independent statistician (who did not take part in assessing the patients at any point in the study) using computer-generated random numbers structured in blocks. The block size information is not specified in the protocol to ensure that investigators are not able to anticipate treatment arm assignment. The randomization ratio is 1:1. The randomization list is maintained by the sponsor. It has been communicated to the splint manufacturer, Medical Z^®^, ensuring a randomized allocation of the sleeves to each included child, on condition of anonymity.

### Sample size estimates

Based on the literature [26,27], the mean value of AHA was estimated at 1.8 logit (standard deviation = 2) in the placebo splint group. In the Gordon study [27], an improvement of 48% was obtained with a hand-arm bimanual intensive therapy administrated during 1 month. Based on this study and considering the duration of our therapy (6 months), we expected an improvement of 60% in favor of the Lycra® sleeve (mean AHA = 0.72 logit). Considering a two-sided Student test without adjustment, 53 patients per arm were needed (power 80%, alpha = 5%). The analysis will be adjusted for baseline AHA value, allowing to improve the design efficiency. Assuming a 0.4 correlation between the 2 measures (baseline and post-treatment) corresponding to a relative efficiency of 1.16, 45 patients were required. One hundred patients (50 in each arm) were planned to consider a 10% rate of non-analyzable data.

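### On its printed inputs, the sample size of 53 per arm (45 after baseline adjustment) falls about one to two points short of 80% power because figures were rounded down

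*Protocol article*

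**What the plan says.** The Protocol article, section Sample size estimates, starts from a control-arm assumption: "the mean value of AHA was estimated at 1.8 logit (standard deviation = 2) in the placebo splint group". The active arm is set at "mean AHA = 0.72 logit". The test is named ("Considering a two-sided Student test without adjustment") and the result is "53 patients per arm were needed (power 80%, alpha = 5" per cent. The requirement is then reduced for baseline adjustment: "Assuming a 0.4 correlation between the 2 measures (baseline and post-treatment) corresponding to a relative efficiency of 1.16, 45 patients were required". Finally, losses are allowed for: "One hundred patients (50 in each arm) were planned to consider a 10% rate of non-analyzable data". The section Trial design confirms equal allocation: "The randomization ratio is 1:1".

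The 45 does not carry the words per arm, but the planned 50 in each arm with 10% loss shows that this is what is meant (50 × 0.9 = 45).

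**The concern.** A sample size described as needed for 80% power should be the smallest whole number that reaches 80%. A quick check of the printed inputs gives slightly more than 53, and the named Student test needs slightly more again than the normal approximation. The low figure feeds the adjusted 45, and the 45 feeds the total of 100. What is at stake is the accuracy of the power statement: the results report would normally carry this justification forward, and any reader can check it from the figures in the paragraph. Whether 1.08 logit is a sensible target, and the direction of the two means, are separate questions not addressed here.

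**Working it through.** **Inputs (all from Sample size estimates, except the allocation ratio from Trial design).** Means 1.8 and 0.72 logit, so the difference is 1.08. SD 2, taken as common to both arms, so the standardised effect is 1.08/2 = 0.54. Two-sided 5%, power 80%, allocation 1:1. Baseline to post-treatment correlation 0.4, stated relative efficiency 1.16, loss 10%.

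**Step 1: reproduce the 53.** Normal approximation per arm:

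n = 2 × (1.95996 + 0.84162)² × 2² / 1.08² = 53.83.

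Rounded up this is 54; cut down it is 53. A one-sided test would give 43, so sidedness does not explain the printed figure. The natural reading is that 53.83 was truncated.

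**Step 2: power around 53, unadjusted.** The Student test column uses the noncentral t distribution with 2n − 2 degrees of freedom and noncentrality 1.08 / (2 × √(2/n)).

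| n per arm | Normal approximation | Student test |
|---|---|---|
| 53 | 79.4% | 78.6% |
| 54 | 80.1% | 79.4% |
| 55 | 80.8% | 80.1% |

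The smallest n reaching 80% is 54 by the normal approximation and 55 by the test that the article names.

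**Step 3: the reduction to 45.** On the article's route, 53/1.16 = 45.7, which rounds up to 46; 45 is printed. The printed 1.16 equals 1 + 0.4². The usual gain from adjusting for baseline is 1/(1 − 0.4²) = 1/0.84 = 1.19, and on that route 53 × 0.84 = 44.5, which does round up to 45. Both routes are carried below. The adjusted SD is 2/√1.16 = 1.857 with the printed efficiency and 2 × √0.84 = 1.833 with 1.19; the t calculation uses 2n − 3 degrees of freedom.

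| n per arm | Efficiency 1.16: normal | Efficiency 1.16: t | Efficiency 1.19: normal | Efficiency 1.19: t |
|---|---|---|---|---|
| 45 | 78.8% | 77.9% | 79.8% | 78.9% |
| 46 | 79.7% | 78.8% | 80.7% | 79.8% |
| 47 | 80.5% | 79.7% | 81.5% | 80.7% |
| 48 | 81.3% | 80.5% | 82.3% | 81.5% |
| 50 | 82.8% | 82.1% | 83.8% | 83.1% |

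At 45, all four variants lie below 80%. By the t test, 80% needs 48 analysable per arm with 1.16, or 47 with 1.19. This agrees with reducing the corrected start directly: 55/1.16 = 47.4, so 48; 55 × 0.84 = 46.2, so 47.

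**Step 4: the loss allowance.** 45/0.9 = 50, so this step is right as printed. Applied to the corrected figures, 48/0.9 = 53.3 gives 54 per arm (108 in total), and 47/0.9 = 52.2 gives 53 per arm (106 in total), against 100 planned.

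**Step 5: the shortfall as a detectable difference.** With 45 analysable per arm and efficiency 1.19, the t test has 80% power for about 1.095 logit rather than 1.08.

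**The case against.** The strongest reply is that this is rounding, not a wrong calculation. The method is recognisable, the printed 53 lies within one or two patients of the right answer, and the power gap is smaller than the uncertainty in the inputs. The SD is printed as 2, without decimals: with an SD of 1.96, 53 per arm would give 80.2% by the t test. Likewise, with efficiency 1/(1 − r²), a correlation of 0.43 instead of 0.40 would give 80.1% at 45 per arm. Enrolment ended in September 2020, so no recruitment decision depends on the point. The 45 arises only if the full 10% is lost.

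Most of this stands, and it sets the size of the point. It does not remove it. The article prints neither an SD of 1.96 nor a correlation of 0.43, and small changes the other way widen the gap (with SD 2.05, 53 per arm gives 76.6%).

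Two stronger readings are tempting, and neither is supported. A reader might infer that the trial is underpowered. The figures show a shortfall of at most about two points at the planned loss, and more than 80% power if all 50 per arm are analysable. A reader might also infer that the 45 is low only because the 53 was low. On the article's own route there is a second rounding down, 45.7 to 45, and the printed efficiency of 1.16 also plays a part. That last element works in the trial's favour once corrected, because 1.19 lowers the number required.

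**Conclusion.** The point holds as a small arithmetic correction. On the article's inputs, 53 per arm gives 78.6% power by the named Student test (79.4% by the normal approximation), and 80% needs 55 (or 54). At 45 analysable per arm, power lies between 77.9% and 79.8% depending on the method and the efficiency used; by the t test it is 77.9% with 1.16 and 78.9% with 1.19. The shortfall is therefore about one to two points by the t test, and as little as 0.2 points by the most favourable normal approximation.

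This rests on an SD of exactly 2 in both arms, a correlation of exactly 0.4, 45 read as per arm, and the full 10% loss. That truncation produced the 53 is an inference from 53.83; the article does not show its working.

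**What to change.** Revise Sample size estimates, with no further enrolment:

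- State 55 per arm for the unadjusted two-sided Student test.
- Then take one of two consistent routes. Either keep the relative efficiency of 1.16, state that 48 analysable per arm are required, and report that 45 give about 78% power. Or correct the relative efficiency to 1/(1 − 0.4²) = 1.19, state 47 analysable per arm, and report that 45 give about 79% power for 1.08 logit (detectable difference at 80% power about 1.095 logit). Stating 47 while leaving 1.16 in place would create a new inconsistency.
- Keep the planned 100 and the 10% allowance as they are. It may be added that 50 analysable per arm would give about 82% (with 1.16) or 83% (with 1.19).

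The cost is wording only; the stated power becomes slightly less favourable. The planned analysis does not change.

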### Population

#### Patient’s eligibility

The inclusion criteria are children with ante-natal or peri-natal hemiplegic cerebral palsy, aged 5 to 10, having social insurance, written informed consent. The exclusion criteria are allergy to Lycra^®^, contra-indication to pressure therapy (e.g., skin lesions, allergic contact dermatitis), behavior or speech troubles, treatment with Botulinum Neurotoxin on the involved arm within the preceding 4 months, children under tutorship or curatorship, and predictable lack of compliance.

Patients may be discontinued from this trial at any time, firstly for voluntary discontinuation. Other specific reasons for discontinuing a patient are the administration of Botulinum Neurotoxin on the involved arm during the study and/or compliance under 80%. Any discontinuation is referred as soon as possible to the principal investigator. Data regarding the discontinued patients will be analyzed in the intention-to-treat analysis.

#### Demographic data

The following demographic data are collected for each participant: age, sex, impaired side, medical history, and current treatments (usual medications, botulinum toxin injections, rehabilitation therapies). The presence of unilateral neglect, presence, and type of cognitive troubles and level of intelligence quotient (IQ) are also collected, as well as the level of scholarship and adaptations needed (special needs assistant for example).

Functional profile of the child is classified using Gross Motor Function Classification Scale (GMFCS) [28] and Manual Abilities Classification System (MACS) [29]. GMFCS is commonly used to describe the gross motor function, notably because it has strong discriminative validity [30]. It focuses on describing gross motor function in self-initiated movements and, in particular, during sitting and walking. The performances of the child are classified according to five levels of functions, from level I which designates independent movement to level V which designates complete assistance. MACS has been developed to categorize how children with cerebral palsy can use their hand when handling objects in daily activities. It particularly points out the child’s use of both hands together and typical manual performance, in opposition to his/her best manual capacity. Similar to GMFCS, MACS consists of five levels which are intended to be clinically meaningful.

### Outcomes

#### Primary outcome: performance measure, Assisting Hand Assessment

The variation of the Assisting Hand Assessment (AHA) from baseline to 6 months is the primary outcome. The AHA is a standardized and criterion-referenced test [31]. It evaluates the performance of children when using their impaired upper extremity during bimanual activities. It reflects what the child really does in his/her daily activities. It is widely used in cerebral palsy evaluation, both in clinical and research purposes. The affected hand is designated as the assisting hand.

The AHA must be administered and scored by a certified occupational therapist. It consists of a 10–15 min video-recorded and semi-structured play session. The child is seated and presented a selection of standardized toys. The scoring is made on the video record, focusing on how the affected hand is used together with the non-affected hand. The detailed criteria are given in the test manual. Quality of performance is scored on a 4-point scale (4 = effective, 3 = somewhat effective, 2 = ineffective, 1 = does not do) for 22 items. Items are divided into 6 categories: general use, arm use, grasp and release, fine motor adjustments, coordination, and pace. In addition, the specific criteria describing behaviors within the categories are defined for each item. Items describe different types of object-related actions of the assisting hand. The total AHA raw score, ranging from 22 (low ability) to 88 (high ability), can be converted into a logit score and a logit-based 0–100 scale based on Rasch analysis [32]. According to Krumlinde [32], the results are expressed in “logit-based AHA-unit” [32]. AHA is a validated assessment, with good inter- and intra-rater reliability (respectively 0.97 and 0.99) [33] and a good sensitivity to change [34].

